### 2.5. Variables

The following variables will be assessed during the study implementation.

#### 2.5.1. Pain

Maximum and mean pain intensity and pain duration: The visual analogue scale (VAS) will be used. It consists of a horizontal line of 10 cm: on the left is the absence or lesser intensity of pain, with 0: “no pain” and on the right the highest intensity, with 10: “the worst pain imaginable”. The patient will be asked to mark on the line the point that indicates the pain intensity that she feels. To know the score, the researcher will measure the distance from “no pain” to the patient’s mark [38,39,40]. The pain classification will be taken as mild pain (1–3 cm), moderate pain (4–6 cm) and severe pain (7–10 cm). The patient should fill in the scale each day of her menstruation indicating the maximum level of pain that she has experienced during each day.Pain severity: The McGill Short Questionnaire (SF-MPQ^®^) will be used. The questionnaire has three parts: the pain rating index; a sensory subscale with 15 items that are classified on an intensity scale where 0 = none, 1 = mild, 2 = moderate and 3 = strong, which ranges from 0 to 45 points; a VAS (ranged from 0 to 10); and the current pain index (a subscale that measures pain intensity from 0 to 5). The higher the SF-MPQ^®^ score, the greater the pain severity [40,41]. The patient should fill in the questionnaire on the day of maximum pain of her menstruation.Number of anti-inflammatory drugs taken by the patients: a diary kept by the researcher will be used. The patients will record each NSAID in the diary, what type and amount of it they take during all the days of their menstruation and whether there has been pain relief with each dose.

Pain will be measured once a month every 6 months and at 3 and 6 months.

#### 2.5.2. Quality of Life

The SF-36v2^®^ Health Questionnaire will be used. It is made up of 35 items that measure 8 dimensions of health-related quality of life. In addition, it includes a change self-assessment item that is not used in scoring. The instrument items cover: physical function, physical role, bodily pain, general health, vitality, social function, emotional role and mental health. The higher the score on the SF-36, the better the health. The “acute” version (1 week) will be used [42,43]. The patient must fill in the questionnaire on the last day of her menstruation. Quality of life will be measured once a month every 6 months and at 3 and at 6 months.

#### 2.5.3. Sleep Quality

The Pittsburgh Sleep Quality Index (PSQI^®^) will be used. It is a self-administered questionnaire that consists of 19 items in addition to 5 questions for the bed partner. The latter are used as clinical information, but do not contribute to the total score of the index. The 19 items analyze different determining factors of sleep quality, grouped into 7 components: sleep quality, latency, duration, efficiency, disturbances, use of sleep medication and daytime dysfunction, where each component is scored from 0 to 3. The sum of the 7 components gives the total score of the PSQI^®^, which ranges between 0 and 21 points: the higher the score, the poorer the sleep quality [44,45]. Buysse et al. [44] propose a cut-off point of 5 (score ≥ 5 defines “bad sleepers”). The patient must fill in the questionnaire on the last day of her menstruation. Sleep quality will be measured once a month every 6 months and at 3 and at 6 months.

#### 2.5.4. Overall Improvement and Treatment Satisfaction

Patient’s Global Impression of Change Questionnaire (PGIC). The questionnaire consists of 7 items. The patient must choose the one that most closely approximates the improvement obtained with the treatment. The higher the score, the worse the impression of change [46]. The patient should fill it in at the end of the treatment and at the end of the reevaluation. Overall improvement will be measured at 5 months and at 11 months.As a subjective measure of the success of the treatment, patients will be asked, using a Likert scale, if they would like to continue with the treatment to maintain the objectives achieved. The scale shows the degree of agreement or disagreement with the treatment. The patient should fill it in at the end of the treatment and at the end of the reassessment. It will be measured at 5 and at 11 months.

#### 2.5.5. Secondary Effects

Possible treatment adverse reactions will be collected, and patients will be asked to fill in a short questionnaire prepared by the investigator after each treatment session. Time frame: Once a week for 12 weeks during treatment and a follow up 11 months after the onset.

### 2.6. Procedures and Timing

The procedure of the study will be established in two arms.

#### 2.6.1. Arm 1, Experimental Group

TTNS group. Participants will receive an intervention session each week over a period of 12 weeks. The total application time will be 30 min. A symmetrical biphasic current will be applied, with a frequency of 20 Hz in continuous mode and an impulse duration of 200 μs. Participants will be placed in the supine position with the soles of the feet together and the knees flexed and abducted at 90°. Two adhesive electrodes will be used for each leg. The first will be 32 mm in diameter and placed on the posterior tibial nerve, 4–5 cm cranial to the internal malleolus, between the posterior edge of the medial border of the tibia and the soleus tendon. The second will be 50 mm × 50 mm and placed in the ipsilateral calcaneus. The electrodes will be connected to a NeuroTrac^®^ PelviTone stimulation device. The stimulation range will be selected according to the tolerable pain limit for the patient, between 1 and 30 mA (adjustable in 1 mA levels). An intensity elevation will be allowed each time the patient perceives the fading of the previous sensation due to accommodation. Under no circumstances should the stimulation cause a painful feeling.

#### 2.6.2. Arm 2, Control Group

One intervention session per week will be performed during a 12-week period time. The total application time will be 30 min. A discontinuous current at 2 Hz frequency and a pulsed frequency of 50 μs, with 2 s of work and 10 s of pause will be applied in other localization. The participant will be placed in the same position. Two 50 mm × 50 mm adhesive electrodes will be placed on the external face of the thigh, on a single leg. This area is outside the territory of the posterior tibial nerve. This simulated current is considered to be insufficient to achieve therapeutic effects in the body and to be outside of the usual ranges. The pain limit level of the patient will be considered for graduating the intensity (1–60 mA, adjustable in 1 mA levels). Patients will experience a low or moderate sensation and no muscle contraction will be achieved.

### 2.7. Data Collection and Management

The data will be collected through self-administered questionnaires. These data will be randomized using the SPSS v26 software (IBM Corporation, Armonk, NY, USA).

### 2.8. Data Analysis

For the statistical analysis, the corresponding statistical tests will be carried out to establish the differences between groups and differences within each group independently. 

The results will be expressed as mean ± standard deviation for the quantitative variables and as a number and percentage for the qualitative variables. Normality will be evaluated with the Kolmogorov–Smirnov test. The mean of the two groups will be compared using a Student’s *t*-test for independent samples or a Mann–Whitney U test as appropriate. Qualitative variables will be analyzed using an x^2^ test. The relationships of the quantitative variables to each other will be tested using the Pearson or Spearman correlation as appropriate. To analyze the effect of the intervention, the results obtained among the intervention group will be compared with those obtained among the control group. A value of *p* < 0.05 will be established as statistically significant.

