#### 2.1.2. The Secondary Objectives Are

To evaluate TTNS effectiveness in reducing NSAIDs in the short term.To evaluate TTNS effectiveness in reducing pain in the short term.To evaluate TTNS effectiveness in improving the quality of life of women with PD in the short term.To evaluate TTNS effectiveness in improving sleep deficiency among women with PD in the short term.To confirm if any decrease in pain is maintained over time.To confirm if any improvement in quality of life is maintained over time.To confirm if any improvement in sleep deficiency is maintained over time.To evaluate patient satisfaction with the treatment.To explore adverse reactions arising from the treatment.

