### 2.4. Sample

It is estimated that the study will have a sample of 60 participants (Figure 1). 

The inclusion criteria for participant selection will be the following: women aged between 18 and 43 years, who have regular menstrual cycles (21–35 days) and who present between 4–10 points of the visual analogue scale (VAS) during half of their menstrual cycles per year and/or during their last three cycles for pain located at the suprapubic area, abdomen, lower lumbar area, perineum and/or medial side of the thighs in the first two days of their menstrual cycle.

The exclusion criteria established will be: women with an intrauterine device implanted or women with hormonal treatment; those diagnosed in the last 18 months of secondary dysmenorrhea by their gynecologist (endometriosis, ovarian cyst, etc.); abdominal or pelvic surgeries during the study or having given a birth in the last 6 months; presence of skin lesions such as scars, erosions, etc., on the upper-internal face of the ankles; pregnancies; and women who have pacemakers, uncorrected coagulopathies, severe comorbid disorder, cancer (in the last 5 years or currently), severe mental disorders or lower-extremity neuropathies and physiotherapy treatments for this pathology one month before the study onset.

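### Within-arm significance tests are planned without a stated limit, and the three maintenance objectives name no contrast with sham, so they could be answered by tests that cannot isolate TTNS

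*Protocol article*

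**What the plan says.** Section 2.8 (Data Analysis) opens by planning statistical tests "to establish the differences between groups and differences within each group independently". It then names the test for comparing the arms: "The mean of the two groups will be compared using a Student’s *t*-test for independent samples or a Mann–Whitney U test as appropriate". No test is named for change within an arm. On the treatment effect it says: "To analyze the effect of the intervention, the results obtained among the intervention group will be compared with those obtained among the control group". A single threshold closes the section: "A value of *p* < 0.05 will be established as statistically significant". It does not distinguish between-group from within-group tests.

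Section 2.1.2 lists three maintenance objectives, for pain, quality of life and sleep. The one for pain reads "To confirm if any decrease in pain is maintained over time"; the other two have the same form. None mentions the control group.

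On the design, section 2.4 gives the sample ("It is estimated that the study will have a sample of 60 participants") and section 2.3 gives 1:1 allocation. Eligibility under section 2.4 covers women "who present between 4–10 points of the visual analogue scale (VAS) during half of their menstrual cycles per year" and/or in their last three cycles. Under section 2.3, baseline questionnaires are completed in the two menstrual periods after the first interview. The control in section 2.6.2 is a simulated current on the thigh that the participant can feel.

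**The concern.** A test of change within one arm asks whether women in that arm differ from their own baseline. It does not use the randomised comparison. Any influence common to both arms (response to a device and weekly contact, change over time, other care) can make it significant when TTNS adds nothing to sham. Significance in one arm and not in the other is no better, because it does not test the difference between the arms.

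The maintenance objectives are the exposed place. A decrease that is maintained can be read as a decrease from baseline among treated women, and the within-arm tests in section 2.8 fit that reading. Durability matters in this trial: the main objective covers the long term, a secondary hypothesis in section 2.2.2 states that the reduction lasts 6 months after treatment, and the Discussion calls long-term follow-up essential for understanding how long effects last. A statement about durability could therefore rest on a comparison that randomisation does not protect.

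**Working it through.** The article gives no power, effect size or SD, so there is no figure of the plan's own to reproduce. The calculation below is an illustration.

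**Inputs from the article**
- 60 women in total (section 2.4), allocated 1:1 (section 2.3): 60 / 2 = 30 per arm.
- Significance level 0.05 (section 2.8).

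**Assumptions**
- Two-sided tests; sidedness is not stated.
- A paired t-test within each arm; the article names none.
- No true difference between TTNS and sham, and independent arms.
- The same mean improvement in both arms, equal to d standard deviations of the change score. A range of d is shown because its size is unknown.

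**Formulas**
- Noncentrality: λ = d × √30.
- Chance that the TTNS arm is significantly improved: p = P(T > 2.045), where T is noncentral t with 29 degrees of freedom and noncentrality λ, and 2.045 is the two-sided 5% critical value.
- Chance that TTNS is significant and sham is not: p(1 − p).
- Chance that exactly one arm is significant: 2p(1 − p).

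| d | λ | p | p(1 − p) | 2p(1 − p) |
|---|---|---|---|---|
| 0 | 0 | 0.025 | 0.024 | 0.049 |
| 0.2 | 1.095 | 0.184 | 0.150 | 0.300 |
| 0.36 | 1.972 | 0.479 | 0.250 | 0.499 |
| 0.5 | 2.739 | 0.754 | 0.186 | 0.371 |
| 0.8 | 4.382 | 0.988 | 0.011 | 0.023 |

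The chance that TTNS alone is significant cannot exceed 0.25, since p(1 − p) peaks at p = 0.5. The row at 0.36 SD sits almost at that maximum and is a worst case. At 0.8 SD the figure is about 1%, because both arms are then nearly always significant.

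**On the VAS scale.** With an assumed SD of change between 2.5 and 1.5 points, a shared fall of 0.5 points makes the TTNS arm significant in 18% to 42% of trials, a fall of 1 point in 56% to 94%, and a fall of 1.5 points in 89% to 100%.

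**Between-group comparison.** A fall shared by both arms cancels in the difference. In the simulation described next, an independent-samples t-test on change from baseline rejected in 4.6% to 5.3% of runs.

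**Regression to the mean.** This was simulated with 4000 replicates, selection on VAS of at least 4, assumed between-woman and within-woman SDs of 1.5, and population means from 4 to 6. If the baseline were the same cycle that qualified the woman, the TTNS arm would be significantly improved in 14% to 64% of trials from regression alone. If the baseline comes from two fresh cycles, the figure is 2% to 3%, close to the 2.5% expected in one direction by chance.

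**The case against.** The strongest reply is that section 2.8 already contains the right comparison. It assigns the effect of the intervention to intervention against control, and the only tests of means that it names are between-group tests. This stands. A reader might infer that the within-arm tests are planned as the evidence of efficacy; the article does not say so, and its own sentence on the treatment effect points the other way. The main objective also covers the long term, so the maintenance objectives can be read as between-group questions. That reading is possible, but section 2.1.2 does not state it, and section 2.8 supplies a within-arm test that would fit the other reading equally well.

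A second tempting inference is that women selected for high pain will improve in both arms through regression to the mean. The design counters most of this. Eligibility rests on past cycles and baseline is recorded in two later ones, so most of the regression should happen before baseline. The exception would be if those two baseline cycles were also used to select women, which the article does not say. The concern therefore rests mainly on placebo response and shared time trends.

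Third, the size of any shared improvement is unknown and need not be the same for every outcome and visit. Within-arm tests can often reach significance without a TTNS effect; it does not follow that they will.

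**Conclusion.** The point holds in a limited form. Within-arm significance tests are planned beside the between-group tests, at the same threshold and with no stated limit on their role, and three objectives are worded so that such tests could answer them. They cannot show that an advantage of TTNS over sham is maintained. Under the stated assumptions, the chance of a significant improvement within the TTNS arm with no true effect runs from 18% (shared improvement of 0.2 SD of change) to 99% (0.8 SD). The chance that TTNS alone is significant is 15%, 25%, 19% and 1% at 0.2, 0.36, 0.5 and 0.8 SD. These percentages depend on the assumed shared improvement and on a paired t-test. That a within-arm test cannot separate TTNS from a shared change depends on neither.

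Severity is minor to moderate, because the valid comparison is already stated for the treatment effect and only needs to be extended explicitly to maintenance.

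**What to change.** In section 2.8, state that changes within each arm are descriptive only: mean with SD or 95% CI, and no p-values. State that both the effect and its maintenance are judged by the TTNS-minus-sham difference at each visit, including 3 and 6 months after treatment, adjusted for the baseline value already collected and reported with a 95% CI.

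In section 2.1.2, reword the three maintenance objectives (pain, quality of life, sleep) as questions about that between-group difference at those visits.

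No visit, questionnaire or participant is added. The cost is a small amount of extra analysis for the baseline adjustment, and fewer small p-values to report.

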## Abstract

Primary dysmenorrhea (PD) is a painful menstruation that can persist for the duration of a woman’s fertile life. Non-steroidal anti-inflammatory drugs, hormonal therapy, physiotherapy techniques, etc., are the main treatments. The main objective of this study is to evaluate the effectiveness of transcutaneous posterior tibial nerve stimulation (TTNS) in PD patients. The study will consist of a single-blind randomized clinical trial, parallel-assigned with two arms. Women with PD (18–43 years) with regular menstrual cycles and at least 4 points in VAS will be randomly divided into experimental (TTNS) and placebo (simulated stimulation) groups during 12 treatment sessions (1 session/week) and several follow-ups: monthly during treatment and 1, 3 and 6 months after. Maximum and mean pain intensity, pain duration, pain severity, number of anti-inflammatory drugs, quality of life, sleep quality, overall improvement, treatment satisfaction and secondary effects will be measured once a month every 6 months and at 3 and 6 months. The Student’s *t*-test for independent samples or the Mann–Whitney U test will be used. The literature shows effective physiotherapeutic techniques for PD in the short term, which do not act on causes and have limitations. The TTNS technique can be used in transcutaneous and percutaneous modalities, with similar effectiveness, but the transcutaneous causes less discomfort. TTNS modulates pain, and long-term benefits could be achieved at low cost and without patient discomfort.

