### 2.3. Design and Setting

This is an experimental study, a single-blind randomized clinical trial with a parallel assignment study with 2 arms, which will be implemented in a physiotherapy center.

The study will consist of four parts:

First interview. The study characteristics will be explained to the participants in a 30-minute interview. A signed informed consent document and a filled-in medical history sheet will be required to participate. This medical history sheet will be filled out by the participant with the support of the researcher during this first interview. It will consist of the following sections: demographic characteristics, life habits, general medical history, gynecological history, obstetric history, menstrual history and history of menstrual pain.

Evaluation phase. Several questionnaires during two consecutive menstrual periods will be filled out. These questionnaires will be given to the participants at the first inter-view and they will have to self-administer them during the following two menstrual periods. The objective of this phase will be to know the baseline status of the participants with respect to the variables studied.

Intervention phase. Participants included in the study will be randomly assigned to two groups, an interventional and a control group, at a 1:1 ratio. Participants will not know which group they belong to. One session a week (12–30 min) will be conducted. Both groups will receive a symmetrical biphasic current in different leg locations. The stimulation will be performed transcutaneously through two/four electrodes at the leg. The technique shall be always painless, without harmful effects. Patients must fill in the questionnaires and on the last day of the treatment a treatment satisfaction scale will be requested. These questionnaires will be self-administered. The satisfaction and global improvement scales will be completed on the last day of treatment in the office, but on an individual basis, without the advice of the researcher. In addition, after each treatment session, participants will fill out a side-effect questionnaire.

Re-assessment phase. The same questionnaires will be filled in a month after treatment, and 3 and 6 months after the treatment ends. In addition, at the end of the 6-month follow-up period, patients will be asked to fill out the adverse effects questionnaire and the satisfaction and global improvement scales again. All these questionnaires will be self-administered.

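### The between-arm test for quantitative outcomes has no baseline term, although two baseline cycles are collected; it is valid but inefficient

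*Protocol article*

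**What the plan says.** Section 2.8 (Data Analysis) names the between-arm method outright: "The mean of the two groups will be compared using" a Student's t-test for independent samples, or a Mann-Whitney U test as appropriate. The Abstract names the same two tests. Section 2.8 describes the treatment effect as a direct comparison: "the results obtained among the intervention group will be compared with those obtained among the control group". No covariate, repeated-measures model or summary over cycles is mentioned. The section also says that "Normality will be evaluated with the Kolmogorov–Smirnov test", that tests will be done "to establish the differences between groups and differences within each group independently", and that "A value of *p* < 0.05 will be established as statistically significant".

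On data collection, section 2.3 (Evaluation phase) says "Several questionnaires during two consecutive menstrual periods will be filled out" before treatment, in order to establish each woman's baseline status on the study variables. The Abstract gives the later measurements as "monthly during treatment and 1, 3 and 6 months after". Section 2.4 gives an estimated sample of 60, and section 2.3 allocates 1:1.

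**The concern.** A woman's pain, quality of life or sleep score in one cycle usually predicts her score in a later cycle. A between-arm test that ignores the earlier score leaves that predictable part in the error term. The trial already collects the earlier score, twice, so the precision is available without further recruitment. It matters here because the sample is small, no power calculation is given, and section 4 (Limitations) warns that the strict entry criteria could limit the planned sample size. What is at stake is an interval wider than the collected data allow, and a real chance of missing a moderate effect.

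The normality rule adds a smaller problem. If a pre-test selects between a comparison of means and a comparison of ranks, the reported effect measure can differ from one outcome or visit to the next.

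**Working it through.** **Inputs from the documents.** 60 women at 1:1, so n = 30 per arm if all complete (sections 2.4 and 2.3); p < 0.05 (section 2.8; sidedness is not stated, two-sided taken); two baseline cycles (section 2.3). There is no stated power figure to reproduce.

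**Assumptions, not in the documents.** A true effect of 0.6 single-cycle SD; the same correlation r between any two cycles, shown at 0.3, 0.5 and 0.7; no dropout; one outcome cycle analysed at a time.

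**Step 1: the stated test.** Set the single-cycle variance to 1. The noncentrality is 0.6 × √(30/2) = 2.32. With 58 degrees of freedom, power is 0.63.

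**Step 2: adjust for the mean of the two baseline cycles.**
- The baseline mean has variance (1 + r)/2 and covariance r with the outcome.
- Residual variance factor: 1 − r² / ((1 + r)/2) = 1 − 2r²/(1 + r).
- r = 0.3: 1 − 0.18/1.3 = 0.862.
- r = 0.5: 1 − 0.50/1.5 = 0.667.
- r = 0.7: 1 − 0.98/1.7 = 0.424.

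**Step 3: a t-test on change from the baseline mean.**
- Variance factor: (1 − r)(1 + 1/2) = 1.5(1 − r), giving 1.05, 0.75 and 0.45.
- This exceeds the factor in Step 2 at each r. It is also worse than ignoring baseline altogether when r is below 1/3.

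**Step 4: power and equivalent sample size.** The effect is divided by the square root of the variance factor; ANCOVA has 57 degrees of freedom.

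| r | ANCOVA variance factor | Change-score variance factor | Power, unadjusted | Power, ANCOVA | Women needed unadjusted for the same precision (60 / ANCOVA factor) |
|---|---|---|---|---|---|
| 0.3 | 0.86 | 1.05 | 0.63 | 0.69 | 70 |
| 0.5 | 0.67 | 0.75 | 0.63 | 0.80 | 90 |
| 0.7 | 0.42 | 0.45 | 0.63 | 0.94 | 142 |

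A simulation at r = 0.5 (4,000 runs) gave 0.64 unadjusted and 0.80 adjusted, in line with the formulae. At a smaller assumed effect of 0.5 SD, power goes from 0.48 unadjusted to 0.54, 0.64 and 0.83 adjusted.

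**Step 5: the normality pre-test.** With 30 exponential observations and estimated mean and SD, simulation shows the uncorrected Kolmogorov-Smirnov test flagging non-normality in about 12% of samples, and the Lilliefors-corrected version in about 78%. Section 2.8 does not say which version is meant. Exponential data are only an illustration; a VAS bounded at 0 and 10 would behave differently.

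**The case against.** The strongest objection is that nothing here is an error. In a randomised 1:1 trial the unadjusted test is unbiased and holds its type I error. Chance baseline imbalance (SD of √(2/30) = 0.26 baseline SD at 30 per arm) is sampling variation that the interval already reflects. This stands. A reader might infer that the planned comparison is invalid or biased; the documents do not support that.

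Second, the article is condensed, and section 2.8 does not say whether raw scores or changes enter the t-test. That is fair, and a change score would recover most of the gain at r = 0.7 (0.45 against 0.42). It does not remove the point, because change scores lose to ANCOVA at every r tried and the test itself is stated, not left open.

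Third, a reader might infer that the baseline and repeated cycles are discarded. They are not: the within-group comparisons would use baseline, and the on-treatment cycles could be tested one at a time. What is missing is baseline in the between-arm contrast.

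Fourth, the gain depends on r. If single-cycle readings are noisy, r is low and the gain is modest: at r = 0.2 the variance factor is 1 − 0.08/1.2 = 0.93 and power about 66%. Nor can noise be read off the entry rule. Section 2.4 requires a VAS of 4 to 10 in half of the year's cycles and/or in the last three, so the second route counts too.

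Finally, how women with missed visits would be handled is commonly left to an analysis plan that is not shown, and no finding is made on it.

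**Conclusion.** The point holds as one of efficiency, and the change should be made. The documents fix an unadjusted between-arm test although the trial collects two baseline cycles per woman. Under the stated assumptions, adjustment cuts the variance by 14%, 33% or 58% at r = 0.3, 0.5 or 0.7 and lifts single-visit power from about 63% to 69%, 80% or 94%. The direction does not depend on the assumed effect, but the size depends on r, which the documents do not give.

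A larger claim is tempting. If three on-treatment cycles are also averaged, the variance factors fall to 0.39, 0.33 and 0.22, and power at 0.6 SD is about 95% or more. That should not be set against the 63%. It is a different estimand, it assumes three cycles and an effect constant from the first of them, and it does not address the comparisons at 1, 3 and 6 months after treatment.

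The normality pre-test is a secondary matter. How poor a switch it is depends on a version the article does not name. The firm part is that it lets the effect measure vary across outcomes and visits.

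**What to change.** In section 2.8, replace the unadjusted between-arm test for quantitative outcomes with a baseline-adjusted comparison, using the mean of the two baseline cycles as covariate. Either ANCOVA at each named time point or a repeated-measures mixed model giving the same contrasts will do. Report the adjusted difference with its 95% confidence interval at the last on-treatment cycle and at 1, 3 and 6 months after treatment.

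Do not let the Kolmogorov-Smirnov test choose the main analysis; keep a rank-based test as a sensitivity analysis for skewed outcomes. An average over on-treatment cycles may be added as a separate, labelled estimand, with a note that it understates the final effect if the effect builds up during treatment.

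The cost is one degree of freedom and analysis wording; no new data or visits are needed. The change should be fixed before unblinded data are seen.

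### Section 2.8 names only an unordered chi-square test for qualitative variables; applied to the ordered satisfaction scale or the PGIC, it would lose much of the power at 30 per arm

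*Protocol article*

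**What the plan says.** Section 2.8 sorts variables into two classes. Quantitative variables are compared between groups by a Student's t-test or a Mann–Whitney U test, with the choice left open. For the other class there is one sentence: "Qualitative variables will be analyzed using an" chi-square test. It gives no choice and names no other test. A p-value below 0.05 "will be established as statistically significant".

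Section 2.5.4 describes two ordered patient-reported scales, both completed at the end of treatment and at the end of follow-up:

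- **PGIC.** The woman picks one of seven options. The article speaks of it as a score with a direction: "The higher the score, the worse the impression of change".
- **Satisfaction.** A Likert item asks whether she would like to continue treatment: "The scale shows the degree of agreement or disagreement with the treatment". The number of levels is not given, and the item is not called a score.

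Neither 2.5.4 nor 2.8 says which class these scales belong to. On size, section 2.4 states: "It is estimated that the study will have a sample of 60 participants". Section 2.3 assigns them to "an interventional and a control group, at a 1:1 ratio".

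**The concern.** A chi-square test on a two-by-k table treats the k categories as labels. Shuffling the order of the columns leaves the statistic unchanged, so it cannot use the fact that one arm sits consistently further towards the better end. It also spreads its sensitivity over k − 1 degrees of freedom: six for a seven-level PGIC, four for a five-level Likert item. The trial's question about these scales is directional: do women given active stimulation report more improvement and more satisfaction?

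The other scales in section 2.5 are numeric: the VAS, SF-MPQ, number of anti-inflammatory drugs, SF-36 and PSQI. The Likert item is therefore a natural candidate for the chi-square sentence, and the PGIC is a possible one. At 30 per arm, a real shift on either scale could be missed because of the choice of test alone. Satisfaction is a named secondary objective in section 2.1.2.

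**Working it through.** The plan gives no power figure for these scales, so there is none to reproduce. The check compares the two tests that section 2.8 already names.

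**Inputs from the article**
- Total sample 60 (2.4), allocated 1:1 (2.3): 60/2 = 30 per arm.
- Significance level 0.05 (2.8). Two-sided is assumed, as the article does not say.
- PGIC: 7 options (2.5.4).

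**Assumed inputs**
- Likert item: 5 levels.
- Control distribution, 7 levels: 5, 10, 20, 30, 20, 10, 5%.
- Control distribution, 5 levels: 10, 20, 30, 25, 15%.
- Treatment effect: a proportional-odds shift with a common odds ratio (OR) of 1 to 4.

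**Step 1. Active-arm distribution.** At each cut point with control cumulative probability c, the active-arm odds are OR × c/(1 − c). For seven levels and OR 3, the first cut is 3 × 0.05/0.95 = 0.158, giving probability 0.158/1.158 = 0.136. Continuing, the active arm has 13.6, 21.0, 27.2, 23.0, 9.7, 3.8 and 1.7%. For five levels it has 25.0, 31.3, 25.6, 12.6 and 5.6%.

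**Step 2. Large-sample check of chi-square power.** The noncentrality is λ = 30 × Σ (p₁ − p₂)²/(p₁ + p₂).
- Seven levels, OR 3: λ = 5.35 on 6 df, power about 36%.
- Five levels, OR 3: λ = 5.30 on 4 df, power about 42%.

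**Step 3. Simulation.** In 20,000 trials per setting, Pearson chi-square was compared with the tie-corrected Mann–Whitney test:

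| Levels | OR | Chi-square | Mann–Whitney |
|---|---|---|---|
| 7 | 1 (no effect) | 3.6% | 5.2% |
| 7 | 2 | 13% | 32% |
| 7 | 3 | 31% | 65% |
| 7 | 4 | 51% | 84% |
| 5 | 1 (no effect) | 4.9% | 4.8% |
| 5 | 2 | 18% | 31% |
| 5 | 3 | 41% | 65% |
| 5 | 4 | 61% | 83% |

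Independent repeats at OR 3 gave about 32% v 64–65% for seven levels and about 40% v 63–65% for five. Simulated chi-square power on seven levels is somewhat below the large-sample 36%, in line with its null rejection rate of 3.6% rather than 5%.

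**Step 4. Sparseness.** With seven levels the average expected count per cell is 30/7 = 4.3. In over 99% of simulated seven-level tables, more than 20% of cells had an expected count below 5. This breaks the usual rule of thumb, but the OR 1 rows show no excess of false positives.

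**The case against.** The strongest reply is that the article never assigns either scale to the qualitative class. Section 2.5.4 calls the PGIC a score, and section 2.8 already offers the Mann–Whitney test for quantitative variables. On that reading the PGIC goes to a rank test and loses nothing. This stands for the PGIC: a reader might infer that chi-square is fixed for it, and the text does not say so. It is weaker for the Likert item, which records degrees of agreement and is not described as a score. The point is therefore conditional.

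A second reply is that the power figures rest on invented distributions and on a proportional-odds shift, a form of effect that suits rank tests. That is correct. The gap appears in every non-null setting tried, but its size is illustrative. Chi-square has roughly half the power on seven levels at OR 2 to 3; the relative loss is smaller at OR 4 and on five levels.

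A reader might go further and infer that chi-square is invalid for sparse adverse-event tables. The documents and the arithmetic do not support that:
- Section 2.5.5 says only "Possible treatment adverse reactions will be collected", and section 2.1.2 aims to explore them. No test is tied to them.
- Enumerating every 30 v 30 table, the true type I error of uncorrected Pearson is 0.003 at a 2% event rate, 0.028 at 5%, 0.054 at 10%, 0.053 at 15% and 0.049 at 20%. The maximum over the rates tried is about 0.054.
- Fisher's exact test is far more conservative: 0.0015 at 5% and 0.009 at 10%.
- Single tables can differ (5 v 0 events: Pearson p = 0.020, Fisher p = 0.052), but that does not make Pearson invalid. A fallback for small cells is a detail commonly left to the analysis plan.

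**Conclusion.** The point holds in a limited, conditional form. Section 2.8 fixes an unordered test for qualitative variables and leaves open whether two ordered scales fall under it. If they do, the loss of power is substantial: at OR 3, about 33 percentage points on seven levels (about 32% v 65%) and about 24 on five (41% v 65%). These sizes depend on the assumed category distributions, the proportional-odds shift, five Likert levels and 30 evaluable women per arm. Type I error is not inflated.

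The consequence is confined to secondary outcomes. The general hypothesis in section 2.2.1 concerns pain, quality of life and sleep, which are measured on numeric scales. This is a minor but worthwhile correction that does not threaten the main conclusion.

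**What to change.** Add to section 2.8, before any unblinded analysis, that the PGIC and the satisfaction item are ordinal. Compare them between arms with the Mann–Whitney test already named there, or with a proportional-odds model reporting a common odds ratio and its 95% confidence interval. The model has the advantage of giving an effect size. Restrict chi-square to nominal variables. Stating the number of Likert levels in 2.5.4 would also help. Naming Fisher's exact test for sparse tables is optional.

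The cost is a sentence or two. No data collection, sample size or visit changes.
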